**Methods:**

This study is a multicenter, randomized controlled trial. A total of 120 patients with mild to moderate hypertension and phlegm-dampness constitution will be recruited and randomly assigned in a 1:1 ratio to the treatment group (acupoint: Zusanli, ST36) or the control group (acupoint: Xuanzhong, GB39). All patients will receive 12 weeks of treatment and a 12-week follow-up period. The primary outcome measure is the change in morning systolic blood pressure from baseline to week 12. The secondary outcome measures include blood pressure–related indicators (morning diastolic blood pressure, average systolic blood pressure, average diastolic blood pressure, nighttime systolic blood pressure, nighttime diastolic blood pressure, and blood pressure circadian rhythm) and short-term blood pressure variability coefficient, all of which will be measured by 24-hour ambulatory blood pressure monitoring. Additionally, cardiac-related indicators measured by 24-hour Holter monitoring, metabolic disorder-related indicators, liver and kidney function indicators, transformed scores of the traditional Chinese medicine phlegm-dampness constitution scale, and the Montreal Cognitive Assessment will also be evaluated.

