### Assessment and Outcomes

#### Overview

Participants will undergo evaluations at weeks 0, 2, 4, 6, 8, 10, 12, and 24 during outpatient visits. Twenty-four-hour ambulatory blood pressure and 24-hour Holter electrocardiogram will be examined at weeks 0, 4, 12, and 24. General information (weight, height, waist circumference, hip circumference, family history, medical history, concomitant medications, and lifestyle behavior), relevant laboratory tests (4 items of lipids, fasting blood glucose, glycosylated hemoglobin, serum insulin, homeostatic model assessment of insulin resistance, homeostatic model assessment of β-cell function, insulin-sensitivity index, triglyceride-glucose index, metabolic score for insulin resistance, liver function, and kidney function), heart function, vascular risk stratification, and scale assessment (TCM phlegm-dampness physique score and the Montreal Cognitive Assessment) will be examined at weeks 0, 12, and 24. Major unconscionable cerebrovascular injury, target organ injury, and moxibustion adverse events will be recorded during the study period.

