#### Primary Outcome Measure

In this study, the primary outcome measure is the morning systolic blood pressure, which will be measured by 24-hour ABPM (assessment at weeks 0 and 12).

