#### Secondary Outcome Measures

##### Blood Pressure–Related Indicators (Measured by 24-Hour ABPM)

Morning diastolic blood pressure, average systolic blood pressure, average diastolic blood pressure, nighttime systolic blood pressure, nighttime diastolic blood pressure, and circadian rhythm of blood pressure will be assessed (at weeks 0, 4, 12, and 24). Twenty-four-hour diastolic blood pressure, 24-hour nocturnal systolic blood pressure, 24-hour nocturnal diastolic blood pressure, 24-hour morning systolic blood pressure, 24-hour morning diastolic blood pressure, circadian rhythm of blood pressure, 24-hour systolic blood pressure variability, and 24-hour diastolic blood pressure variability will also be assessed at different time points (at weeks 0, 4, 12, and 24)

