Potential center effects will be statistically addressed through mixed-effects modeling, notwithstanding standardized central screening and intervention procedures. For primary continuous outcomes, linear mixed-effects models will incorporate the treatment group as a fixed effect and center as a random effect, with center-specific random intercepts accounting for recruitment-related heterogeneity. Secondary outcomes will be analyzed using analogous generalized linear mixed models. The primary analysis will use an intention-to-treat approach. The changes in the primary outcome and other secondary outcomes will be compared by using a linear mixed-effects model with group-by-time point interaction (baseline to week 12). For outcomes measured at multiple time points, a repeated-measures ANOVA will first test for overall group, time, and interaction effects. Upon finding a significant interaction (exact *P* values will be reported), post hoc comparisons will be conducted using a hierarchical adjustment strategy: Benjamini-Hochberg false discovery rate control for the primary outcome across time points and Bonferroni correction for families of secondary outcomes. Sociodemographic and clinical characteristics at baseline will be examined for potential group differences by 2-tailed *t* test or χ^2^ test, with exact *P* values reported. Compliance will be presented using descriptive statistics. The specified significance levels (0.025 for the primary outcome and 0.05 for all other analyses) represent the α thresholds (*P* value cutoffs) for hypothesis testing. All *P* values will be reported per journal style: expressed to two digits (or three if *P*<.01) and as *P*<.001 if below that threshold. Data analysis was conducted with SPSS (version 28.0; IBM Corp).

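### The single week-12 primary comparison is given several analyses, one of them gated by an ANOVA interaction and Benjamini-Hochberg adjusted, and the protocol does not say which decides the trial

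*Protocol article*

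**What the plan says.** The Methods paragraph of the abstract fixes the endpoint: "The primary outcome measure is the change in morning systolic blood pressure from baseline to week 12". The Primary Outcome Measure section agrees, naming only weeks 0 and 12. The Sample Size Calculation treats this as one comparison of two means: expected difference 7.2 mm Hg, SD 3.3 mm Hg, superiority margin 5 mm Hg, one-sided alpha 0.025, power 90%.

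The same variable is collected more often. The assessment Overview says: "Twenty-four-hour ambulatory blood pressure and 24-hour Holter electrocardiogram will be examined at weeks 0, 4, 12, and 24". The list of secondary blood pressure outcomes includes "24-hour morning systolic blood pressure, 24-hour morning diastolic blood pressure, circadian rhythm of blood pressure" at those same weeks.

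The Statistical Analysis section offers the primary outcome three routes:

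- a linear mixed model with treatment group as a fixed effect and centre as a random effect;
- a "linear mixed-effects model with group-by-time point interaction (baseline to week 12");
- for outcomes measured at several times, "a repeated-measures ANOVA will first test for overall group, time, and interaction effects". If the interaction is significant, "post hoc comparisons will be conducted using a hierarchical adjustment strategy: Benjamini-Hochberg false discovery rate control for the primary outcome across time points".

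Neither mixed model carries a gate. The threshold given for the primary outcome is 0.025, without repeating that it is one-sided.

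**The concern.** A comparison at one time point has no family of time points to adjust over, and one prespecified contrast needs no omnibus test before it. By naming the primary outcome in the adjusted step, the Statistical Analysis section conflicts with the endpoint definition and with the sample size calculation.

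Three things are at stake. First, the same data could give different primary conclusions depending on the route taken, and the protocol does not settle which one counts. Second, the interaction F test is non-directional and tests for any difference in time profiles against zero, so it cannot establish superiority by more than 5 mm Hg. Third, on the adjusted route the week-12 threshold moves with the week 4 and week 24 results, and the stated 90% power makes no allowance for that.

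**Working it through.** **Inputs.** From the Sample Size Calculation: difference 7.2, SD 3.3, margin 5, one-sided alpha 0.025, power 90%. From the abstract: 120 patients, 1:1, so 60 per arm. From the Overview: ambulatory monitoring at weeks 0, 4, 12 and 24. Assumed, because the article does not give them: the adjusted family is weeks 4, 12 and 24; the loss is 20%; the effects at weeks 4 and 24 and the correlation over time are as varied below.

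**The plan's own figure.** The distance from the margin is 7.2 − 5 = 2.2 mm Hg.

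n per arm = 2 × (1.960 + 1.282)² × 3.3² / 2.2² ≈ 47.3, rounded up to 48, or 96 in total.

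The stated 120 does not follow from these inputs alone, but 48 / 0.8 = 60 per arm, so it fits them with a 20% allowance. Both 60 and 48 per arm are therefore carried forward.

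**Single ungated week-12 test.** Power = Φ(2.2 / SE − 1.960), with SE = 3.3 × √(2/n).

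- 60 per arm: SE = 0.602, 2.2 / SE = 3.65, power = Φ(1.69) = 95.5%.
- 48 per arm: SE = 0.674, 2.2 / SE = 3.27, power = Φ(1.31) = 90.4%.

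**Benjamini-Hochberg over three visits at 0.025.** The ordered P values are compared with 0.025/3 = 0.0083, 0.025 × 2/3 = 0.0167 and 0.025. If neither other week is significant, week 12 must reach 0.0083 (critical value 2.394). If both others are at or below 0.025, week 12 needs only 0.025.

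- 60 per arm, strictest threshold: Φ(3.65 − 2.394) = 89.6%.
- 48 per arm, strictest threshold: Φ(3.27 − 2.394) = 80.8%.

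If the family held only two visits, the strictest threshold would be 0.0125, giving 92.1% and 84.7%.

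**Simulation of the full gated route.** Four time points, compound-symmetric and autoregressive-type correlation, effect 7.2 mm Hg at week 12, tests against the 5 mm Hg margin:

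| Effect at weeks 4 and 24 | n per arm | Gate passes | Single test | Gate plus adjustment |
|---|---|---|---|---|
| None or half-sized | 60 | 100% | 95% | 88–89% |
| None or half-sized | 48 | 100% | 89–90% | 79–80% |
| Same as week 12 | 60 | 100% | 95% | 94–95% |
| Same as week 12 | 48 | 100% | 90% | 88% |

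**Smaller true effects.** Set the effect so that a test against zero has 90% power: 3.3 × √(2/n) × 3.24, which is 1.95 mm Hg at 60 per arm and 2.18 at 48. Gate plus adjustment then gives about 73–86% with the gate at 0.05, and about 64–84% with the gate at 0.025. These effects are less than a third of the planned 7.2 mm Hg.

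**Error rate.** An adjusted P value is never below the raw one. With no effect at any visit, and testing against zero, the simulated week-12 false positive rate is 0.74% under gate plus adjustment, against 2.5% for the single test.

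**The case against.** The strongest reply is that the gated route may not be the primary analysis at all. The section describes an ungated mixed model over baseline to week 12 for the primary outcome, reserves the ANOVA for outcomes measured at several times, and calls what follows it post hoc. If only weeks 0 and 12 entered the ANOVA, its interaction would be equivalent to the usual comparison of change scores against zero. This stands as far as it goes: that the week-12 test is conditional is one reading, not a certainty. But the adjusted step names the primary outcome and several time points outright, and with week 12 alone that instruction would have no content. The text still does not say which route decides.

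A reader might infer more than the documents support on three counts.

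- *A severe loss of power.* This needs a true effect near 2 mm Hg tested against zero. At the planned effect the gate always passes, and at 60 per arm power stays close to the promised 90%.
- *Week 4 or week 24 alone counting as primary success.* No section says so, and the endpoint stays defined at week 12. The wording only leaves room to report such a result under the primary outcome's name.
- *Patients with a missing visit being dropped.* Classical repeated-measures ANOVA does this if nothing is imputed, but the section bases the primary analysis on an intention-to-treat full analysis set and provides for imputation where needed. Listwise loss is not stated.

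**Conclusion.** The point holds as a conflict between the stated analysis and the stated design. One week-12 comparison is defined and powered, while the analysis text gives it competing routes, one of them gated and adjusted across time points, without naming the one that decides.

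The size is modest at the protocol's own assumptions. The gate costs nothing. The adjustment costs about 6 points at 60 per arm (95% to 89%) and about 10 to 11 points at 48 per arm (90% to 79%) when the other weeks fall short of the margin, and about 1 to 2 points when the effect is equal at all visits. These figures rest on an assumed family of three post-baseline visits and, for 48 per arm, an assumed 20% loss. The cost grows only if the true effect is much smaller than planned.

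The adjusted route is conservative for week 12, so false positives at the defined endpoint are not the problem. The problem is an unidentified deciding test, a gate that cannot test the margin, and a power cost with no purpose.

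**What to change.** In the Statistical Analysis section, name one primary analysis: the ST36 minus GB39 contrast in morning systolic pressure change at week 12, from the linear mixed-effects model in the full analysis set, tested once at one-sided 0.025 against the 5 mm Hg margin used in the Sample Size Calculation. State that it has no ANOVA gate and no Benjamini-Hochberg adjustment. Drop the repeated-measures ANOVA for the primary outcome, and list morning systolic pressure at weeks 4 and 24 as secondary.

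The cost is analysis wording only: no change to visits, data or sample size. The Results section says that no analysis has been performed, so the change can still be made and dated before the data are analysed.

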##### Cardiac-Related Indicators (Measured by 24-Hour Holter Electrocardiogram)

Total heartbeats, myocardial oxygen consumption, average heart rate, heart rate variability (HRV) parameters (ie, percentage of successive NN intervals that differ by more than 50 ms, HRV triangular index, root mean square of successive differences, SD of normal-to-normal [SDNN] intervals, SD of the average normal-to-normal intervals, SDNN index, low-frequency [LF] power, high-frequency [HF] power, and the LF and HF ratio) will be assessed at weeks 0, 4, 12, and 24.

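### Holm's step-down procedure would control the same familywise error as the Bonferroni correction fixed for the secondary families and would never reject less: a minor, nearly free improvement

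*Protocol article*

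**What the plan says.** The Statistical Analysis section of the protocol article describes a sequence for outcomes measured at several time points. A repeated-measures ANOVA comes first. "Upon finding a significant interaction", post hoc comparisons follow: Benjamini-Hochberg for the primary outcome across time points, and "Bonferroni correction for families of secondary outcomes". The significance levels are "0.025 for the primary outcome and 0.05 for all other analyses". On reporting, the section speaks of P values ("All *P* values will be reported per journal style"). It mentions no simultaneous confidence intervals and no step-down variant.

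The section does not define the families. The secondary outcome lists are long. The blood pressure list starts with "Morning diastolic blood pressure, average systolic blood pressure, average diastolic blood pressure, nighttime systolic blood pressure, nighttime diastolic blood pressure", and its members "will be assessed (at weeks 0, 4, 12, and 24"). The Holter list starts with "Total heartbeats, myocardial oxygen consumption, average heart rate, heart rate variability (HRV) parameters". The laboratory list adds lipid, glucose and insulin measures and indices derived from them.

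**The concern.** Single-step Bonferroni holds every member of a family of size m to 0.05/m, even after other members have been rejected. Holm relaxes the threshold as rejections accumulate, needs no assumption about correlation and keeps the same familywise guarantee. Where the reported result is a set of adjusted P values, Holm is at least as good on every data set.

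The question matters somewhat here because the article's Objective includes protection of heart and brain. The evidence for that lies in secondary outcomes, and the sample is set at 120. Many members of a list are related by construction, for instance the SDNN-type measures, LF, HF and their ratio, or the insulin-resistance indices. If the treatment works, several may move together, and that is the situation in which Holm gains most. What is at stake is how many members of a family can be declared once one has been.

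**Working it through.** The article gives no figure for secondary power, so there is nothing of the plan's own to reproduce on this point.

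**Inputs from the article.** "A total of 120 patients with mild to moderate hypertension", allocated 1:1, so 120/2 = 60 per arm (Abstract, Methods). Level 0.05 for non-primary analyses (Statistical Analysis).

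**Assumptions.** Two-sided tests, equal correlation of 0.5 between members, standardised effects of 0.3, 0.4 or 0.6 SD, no dropout and no interaction gate. Family size is also an assumption. If each listed domain were one family, there would be 8 distinct secondary ABPM measures (duplicates and the primary removed), 12 Holter measures and 12 lipid and glycemic measures. If a family were one outcome's post-baseline visits (weeks 4, 12 and 24), m would be 3.

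**Step 1: Holm never rejects less.** Bonferroni rejects if p ≤ 0.05/m. Holm orders the P values and compares the i-th smallest with 0.05/(m − i + 1), stopping at the first failure. For m = 12 the thresholds are 0.05/12 = 0.0042, 0.05/11 = 0.0045, and so on up to 0.05. Every Holm threshold is at least 0.05/m. So if j members satisfy p ≤ 0.05/m, they are the j smallest and all pass.

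**Step 2: same error control.** Let m0 members be true nulls. When Holm first rejects one of them, at most m − m0 members have gone before, so the threshold is at most 0.05/m0. The union bound gives m0 × 0.05/m0 = 0.05, whatever the correlation.

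**Step 3: the first rejection is identical.** Both methods compare the smallest P value with 0.05/m.

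**Step 4: size of the gain.** Bonferroni power per outcome is Φ(d√(n/2) − z), where z is the upper 0.025/m normal quantile. With n = 60, √(60/2) = 5.477, so d√(n/2) is 3.286, 2.191 and 1.643 for 0.6, 0.4 and 0.3 SD. For m = 12, z = 2.865; for m = 3, z = 2.394. For example, at 0.6 SD and m = 12, Φ(3.286 − 2.865) = Φ(0.421) = 66.3%. This does not depend on how many other members are affected. Holm power comes from simulating correlated normal test statistics (200,000 families per row).

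| Family | Affected | Effect | Bonferroni, per outcome | Holm, per outcome | At least one rejection, either method |
|---|---|---|---|---|---|
| 12 | 12 | 0.6 SD | 66.3% | 78.2% | 97.5% |
| 12 | 12 | 0.4 SD | 25.0% | 31.2% | 72.0% |
| 12 | 12 | 0.3 SD | 11.1% | 13.5% | 46.1% |
| 12 | 6 | 0.6 SD | 66.3% | 69.8% | 94.9% |
| 12 | 6 | 0.4 SD | 25.0% | 26.9% | 61.2% |
| 12 | 3 | 0.4 SD | 25.0% | 25.6% | 47.8% |
| 3 | 3 | 0.4 SD | 42.0% | 48.5% | 67.0% |

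No Bonferroni rejection was lost by Holm in any row. With 6 of 12 affected at 0.6 SD, the chance of rejecting at least one true null rose from 0.022 to 0.032, still within 0.05.

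**The case against.** The strongest reply is that nothing here is wrong. Bonferroni is valid, needs no assumption about dependence, and touches neither the primary outcome nor the sample size. This stands: the point concerns efficiency, not error control.

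Second, a reader might infer that Bonferroni decides whether any cardiac, metabolic or circadian effect can be claimed at all. It does not, because the chance of at least one rejection in a family is the same under both methods.

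Third, a reader might take the 12-point gain as the expected one. The article gives no effect size for any secondary outcome, and 0.6 SD on every member is a favourable case. For the metabolic measures the Discussion points the other way, since it reports that the control acupoint also improved metabolic disorders in preliminary observations. Large differences between arms across that whole list cannot be presumed. Nor does the article make confirmation of every member of a family an aim.

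Fourth, families of 8 and 12 are a reading of the outcome lists. The plan does not set them, and the Bonferroni clause could equally cover the time points of a single outcome. The interaction gate, left out of the calculation, would change the power figures. It does not alter the ordering: for any family that passes it, with the same m, Holm still rejects at least as much.

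Last, Bonferroni has simple simultaneous confidence intervals that agree with its tests, and Holm does not. That would be a reason to keep Bonferroni if such intervals were planned. The article mentions none, but it is a real cost of the change, so it goes too far to say that power is given away for nothing.

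**Conclusion.** The point holds as a minor improvement. For the adjusted P values that the article describes, Holm gives the same familywise guarantee and never fewer rejections. This follows from the definitions and rests on no assumption about effect size, correlation or family structure.

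The size of the benefit does rest on assumptions. Over the scenarios shown it runs from 0.6 points of power per outcome (3 of 12 affected, 0.4 SD) to 11.9 points (12 of 12 affected, 0.6 SD). It is small when few members are affected or effects are modest. The documents do not support reading this as an invalid analysis, or as a barrier to showing any secondary effect.

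**What to change.** In Statistical Analysis, replace the Bonferroni correction for secondary families by the Holm step-down procedure (sequential Bonferroni) within each family, at two-sided familywise 0.05. Keep the interaction gate as it stands. Date the change before any analysis; the Results section states that none has been performed.

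The cost is a wording change: Holm-adjusted P values need only sorting and multiplication, and sample size and primary analysis are unaffected. The downside is that 95% confidence intervals beside the adjusted P values would be unadjusted and must be labelled so, because an interval may exclude zero while its adjusted P value is not significant.

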## Results

The study was registered on July 5, 2024, with the Chinese Clinical Trial Registry (ChiCTR2400086582). Data collection began in June 2023 and ended in February 2025. Currently, data from this trial are in the collection phase, and no data analysis has been performed. As of January 2025, we have collected data from 118 patients. The results of this trial are expected to be submitted for publication in May 2026.

## Discussion

### Anticipated Findings

This study aims to explore the acupoint specificity and clinical efficacy of moxibustion in treating hypertension and its protective effects on the heart and brain. In this study, we employed the Montreal Cognitive Assessment to quantitatively evaluate cognitive protection. Hypertension contributes to cerebral microvascular injury and silent cerebral small vessel disease, which predominantly impairs cognitive domains sensitively captured by the Montreal Cognitive Assessment, including executive function and attention. By streamlining acupoint selection and establishing a standardized home-based moxibustion protocol, this study seeks to offer patients with hypertension a safe, convenient, and adherent treatment option. This approach may help patients develop healthy lifestyle habits, contributing positively to the improvement of their quality of life and the prevention of cardiovascular and cerebrovascular diseases.

In TCM, body constitution is considered a determining factor in disease onset and progression. In today’s fast-paced society, factors such as high stress, poor dietary habits, and lack of exercise contribute to the development of a phlegm-dampness constitution. Research has shown that this constitution is a high-risk factor for hypertension and its related complications. Patients with phlegm-dampness hypertension are more prone to insulin resistance, which increases the risk of target organ damage [23], leads to a higher cardiovascular risk over 10 years, and is associated with a poorer prognosis [24]. Molecular genetics research indicates that genes expressed in individuals with phlegm-dampness constitution are similar to those associated with obesity and metabolic syndrome [25]. Therefore, improving phlegm-dampness constitution is crucial for controlling hypertension and preventing cardiovascular and cerebrovascular diseases [26].

The Zusanli acupoint (ST36) is a He-Sea point and lower He-Sea point of the Stomach Meridian, known for its functions of regulating Qi and blood, harmonizing the stomach, and eliminating dampness. X-ray phase-contrast imaging studies have shown that the 3D structure of Zusanli has a higher density of local blood vessels [27], mast cells [28], and prokineticin receptor 2–expressing cells [29] compared with nonacupoints or other acupoints, along with accumulation of elements like calcium, iron, and zinc [30]. The capsaicin receptor (TRPV1) is abundantly present in the mast cells at Zusanli [31], and moxibustion heat at 43 to 46 °C can activate TRPV1 ion channels, mediating mast cell degranulation and releasing bioactive substances that exert antihypertensive effects [32]. Additionally, moxibustion at Zusanli can inhibit immune-inflammatory responses, counter oxidative stress, regulate mitochondrial function and cellular autophagy, enhance blood circulation, and regulate metabolic disorders. Our preliminary clinical observations indicated that although moxibustion at Xuanzhong (GB39) did not significantly lower blood pressure, it did improve metabolic disorders and sleep quality. Therefore, this trial uses Xuanzhong as the control group (rather than a blank or nonacupoint control) to observe the differential efficacy of the 2 acupoints while helping participants develop good moxibustion habits, providing an effective way to prevent and manage chronic diseases [13].

Acute cardiovascular and cerebrovascular events frequently occur in the morning, and numerous clinical studies have confirmed that morning hypertension is an independent predictor of such events [2], positively correlating with their incidence and mortality [33]. For every 1 mm Hg increase in morning blood pressure, the risk of cardiovascular-related death increases by 2.1% [34,35]. Compared with patients with morning blood pressure below 125 mm Hg, those with morning hypertension have significantly higher risks of stroke [36] (hazard ratio 6.01) and coronary events (hazard ratio 6.24). Stroke risk is positively correlated with morning systolic blood pressure levels, with hazard ratios of 2.45, 2.80, 3.58, and 6.52 for morning systolic blood pressure ranges of 135 to 144 mm Hg, 145 to 154 mm Hg, 155 to 164 mm Hg, and ≥165 mm Hg, respectively [37]. Regardless of clinical blood pressure levels, patients with morning home systolic blood pressure ≥145 mm Hg have higher cardiovascular risk (hazard ratio 2.47) than those with levels <125 mm Hg [38]. Morning hypertension is also a significant cause of vascular cognitive impairment [39]. It is an independent risk factor for the 10-year incidence of atherosclerotic cardiovascular disease [40]. Patients with nondipper (0%-10%) or reverse-dipper (<0%) nocturnal blood pressure rhythms have higher risks of cardiovascular events and all-cause mortality [41], as well as a greater likelihood of reduced glomerular filtration rate and elevated creatinine levels [42]. Blood pressure variability, which reflects fluctuations in blood pressure within a certain range, is an important indicator of blood pressure stability. Individuals with higher short-term blood pressure variability, as measured by 24-hour ABPM, are more likely to develop subclinical organ damage and adverse cardiovascular events [43].

Autonomic nervous dysfunction can lead to altered circadian rhythms of blood pressure and increased blood pressure variability, exacerbating damage to vascular endothelium and arterial baroreceptors, accelerating vascular wall fibrosis and atherosclerosis, and ultimately causing target organ damage [44]. HRV, which measures differences between adjacent heartbeats, reflects autonomic nervous activity and inflammation, and is related to coronary physiology [45] and the severity of coronary artery disease [36]. Reduced HRV is closely associated with various cardiovascular diseases, diabetic microvascular complications, and imbalanced body constitutions [46]. SDNN, SD of the average normal-to-normal intervals, root mean square of successive differences, LF, and HF values were significantly lower in patients with hypertension and poorly controlled blood pressure and were independent risk factors for uncontrolled blood pressure [36]. Additionally, prolonged elevated arterial blood pressure increases myocardial oxygen consumption and cardiac workload, leading to myocardial ischemia and cardiovascular diseases, such as coronary heart disease and left ventricular hypertrophy. Evaluating total heartbeats, average heart rate, myocardial oxygen consumption, HRV indices, ischemic ST-T changes, and arrhythmias through 24-hour Holter electrocardiogram is crucial for the early diagnosis of occult coronary artery disease and the prevention and management of acute cardiovascular diseases [36].

Insulin resistance is a common pathophysiological mechanism underlying hypertension, type 2 diabetes, metabolic syndrome, and cardiovascular diseases [47]. It often leads to metabolic, structural, and functional abnormalities in organs and tissues, such as microvascular disease and atherosclerosis, and is an independent risk factor for cardiovascular diseases [48]. The metabolic score for insulin resistance index, which integrates fasting blood glucose, lipids, and BMI, is a novel insulin index that significantly correlates with the incidence of hypertension, angina, heart failure, and myocardial infarction, making it a risk factor for coronary artery disease and the severity of coronary artery lesions [49].

